#### 2.5.4.3.5 Determination of breast-milk intake

Breast milk intake will be determined by a deuterium oxide-dose-to-the-mother method as described previously[96]. Mothers of participating children will be asked to drink a dose of 30g of deuterium oxide (99.8% purity) after the collection of baseline saliva for the mother and the child. Mother/child post-dose saliva will be collected on days 1, 2, 3, 4, 13 and 14. Saliva samples will be analyzed for deuterium oxide enrichment using Fourier Transformed Infrared Spectrophotometer at the Kenya Medical Research Institute (KEMRI). Well-nourished age and gender matched from the community will serve as control.

#### 2.5.4.3.6 Determination of haemoglobin concentration

The Haemoglobin concentration will be determined at baseline and at discharge using capillary blood collected by finger prick with portable HemoCue®AB spectrophotometer (Ängelholm, Sweden). The device will be calibrated on daily basis using a HemoCue Control Cuvette.

#### 2.5.4.3.7 Determination of amino acid profile

Plasma samples for amino acid analysis will be obtained using EDTA as an anticoagulant. Blood samples will be immediately stored on wet ice to prevent micro-hemolysis and transported within 4 hours to the University of North Carolina (UNC) project laboratory for centrifugation and stored maximum at  $-20^{\circ}\text{C}$  until shipping in bulk to the laboratory abroad. Measurement of amino acid concentrations will be performed using an automatic amino acid analyser at Ajinomoto Lab in Japan.

#### 2.5.4.3.8 Determination of stools calprotectin

A single child stools sample collected in a plastic pot upon arrival at the CBCC site at admission, 28 days after starting treatment and at discharge will be used. Faecal calprotectin will be determined using a quantitative point-of-care chromatographic immunoassay kit (Quantum Blue®, Alpha laboratories, Hampshire, UK). As per manufacturer's instructions, two drops of homogenised stool will be applied inside a plastic cassette and the cassette inserted into a portable electronic reader that will display numerical value representing calprotectin concentration. The cassette reader will be calibrated for each day of tests.

#### 2.5.4.3.9 Determination of other biological parameters

At admission and discharge, venous blood sample will also be collected for measurement of acute inflammation (CRP, ESR, and inflammatory cytokines), biological protein indicators (albumin), lipid profile (cholesterol and triglycerides), liver function (ALT, AST) as well as micronutrient status (iron, ferritin and zinc) of the enrolled children. Blood samples will be collected using sterile and disposable butterfly needle by a trained phlebotomist from the paediatric ward of the Baylor Clinic located at Lilongwe[97]. For the analysis to be performed in Malawi, sample management, transportation and preparation for analysis will be done according to the standard

procedures as per World health Organisation guidelines and according to procedures used by the Malawi laboratory of the UNC project. For analysis to be performed abroad, samples will prepared for storage and stored according to the requirement of each test. Samples will stored at -70°C until analysis or if not possible at -20°C. Samples post analysis will also be stored to allow for future analyses. The duration of pot-test samples storage will be 5 years.

#### ***2.5.4.4 Data to be collected***

Data will be collected on a specially designed study form that will be adapted from the standard Outpatient Therapeutic Programme form included in the national guidelines for the management of acute malnutrition. The form will record administrative, nutrition and morbidity data at admission, during recovery and at discharge. The table 4 below provides an overview of the data to be collected and the schedule of their collection.

**Table 4: Data to be collected at admission, during nutrition rehabilitation and during follow up after discharge**

| Variable                                 | Schedule  |                                 |        |           |           |          |                           |    |    |     |       |
|------------------------------------------|-----------|---------------------------------|--------|-----------|-----------|----------|---------------------------|----|----|-----|-------|
|                                          | Admission | During nutrition rehabilitation |        |           |           |          | Follow up after discharge |    |    |     |       |
|                                          |           | daily                           | Weekly | Bi-weekly | Discharge | other    | M3                        | M6 | M9 | M12 | other |
| Socio-demographic data            |           |                                 |        |           |           |          |                           |    |    |     |       |
| Adress                                   | X         |                                 |        |           | X         |          | X                         | X  | X  | X   |       |
| Mother socio-demographic                 | X         |                                 |        |           | X         |          | X                         | X  | X  | X   |       |
| Father socio-demographic                 | X         |                                 |        |           | X         |          | X                         | X  | X  | X   |       |
| Household data                           | X         |                                 |        |           |           |          | X                         | X  | X  | X   |       |
| Natural hazard/Disaster                  |           |                                 |        |           |           | WO       |                           |    |    |     | WO    |
| Man made hazard/Disaster                 |           |                                 |        |           |           | WO       |                           |    |    |     | WO    |
| Nutrition data                    |           |                                 |        |           |           |          |                           |    |    |     |       |
| Oedema                            | X         | X                               |        |           |           |          | X                         | X  | X  | X   |       |
| Weight                                   | X         | X                               |        |           |           |          | X                         | X  | X  | X   |       |
| MUAC                                     | X         | X                               | X      |           |           |          | X                         | X  | X  | X   |       |
| Height                                   | X         |                                 |        | X         |           |          | X                         | X  | X  | X   |       |
| RUTF intake/appetite                     | X         | X                               |        |           |           |          |                           |    |    |     |       |
| Home food intake                         | X         | X                               |        |           |           |          |                           |    |    |     |       |
| Hemoglobin                               | X         |                                 |        |           | X         |          |                           |    |    |     |       |
| Body fat mass                            | X         |                                 |        |           | X         | W2       |                           |    |    |     |       |
| Fat Free mass                            | X         |                                 |        |           | X         | W2       |                           |    |    |     |       |
| Bioelectrical Impedance Analysis  |           |                                 |        |           |           |          |                           |    |    |     |       |
| Phase Angle                              | X         |                                 |        |           | X         | W2       |                           |    |    |     |       |
| Welness Marker                           | X         |                                 |        |           | X         | W2       |                           |    |    |     |       |
| clinical and morbidity data       | X         |                                 |        |           |           |          |                           |    |    |     |       |
| Fever                                    | X         | X                               |        |           |           |          |                           |    |    |     |       |
| Cough/fast or difficulty in breathing    | X         | X                               |        |           |           |          |                           |    |    |     |       |
| Diarrhea/vomiting/dehydration            | X         | X                               |        |           |           |          |                           |    |    |     |       |
| Adbdominal pain                          | X         | X                               |        |           |           |          |                           |    |    |     |       |
| Flatulence                               | X         | X                               |        |           |           |          |                           |    |    |     |       |
| Skin eruption                            | X         | X                               |        |           |           |          |                           |    |    |     |       |
| antibiotic prescription                  | X         | X                               |        |           |           |          |                           |    |    |     |       |
| Malaria parasites                        | X         | X                               |        | X         |           | Fever    |                           |    |    |     |       |
| Stools parasites                         |           | X                               |        |           |           | Diarrhea |                           |    |    |     |       |
| HIV test                                 | X         | X                               |        |           |           |          |                           |    |    |     |       |
| Tuberculosis diagnosis                   | X         | X                               |        |           |           |          |                           |    |    |     |       |
| Discharge data                    |           |                                 |        |           |           |          |                           |    |    |     |       |
| Type of Discharge                        |           |                                 |        | X         |           |          |                           |    |    |     |       |
| Date                                     |           |                                 |        | X         |           |          |                           |    |    |     |       |
| Vital status after discharge (mortality) |           |                                 |        |           |           |          | X                         | X  | X  | X   | X     |
| Community controls                |           |                                 |        |           |           |          |                           |    |    |     |       |
| MUAC                                     |           |                                 |        |           | X         |          |                           |    |    |     |       |
| Weight                                   |           |                                 |        |           | X         |          |                           |    |    |     |       |
| Height                            |           |                                 |        |           | X         |          |                           |    |    |     |       |
| Body fat mass                            |           |                                 |        |           | X         |          |                           |    |    |     |       |
| Fat Free mass                            |           |                                 |        |           | X         |          |                           |    |    |     |       |
| Phase Angle                       |           |                                 |        |           | X         |          |                           |    |    |     |       |
| Wellness Marker                          |           |                                 |        |           | X         |          |                           |    |    |     |       |
| Vital status (mortality)/verbal autopsy  |           |                                 |        |           | X         |          |                           |    |    |     |       |

#### 2.5.4.5 Data recording

Data will be collected on a standardised Outpatient Therapeutic Programme forms adapted from the National OTP cards. Individual patient data will be double entered into a database specially designed for this study by two different data entry clerk. Field supervisors will cross-check data collection forms for completeness and filling quality and will check data entry quality by checking 10% of the entry of the month.

### 2.5.5 Therapeutic foods and patient care

The table 5 below provides the composition of all study RUTFs. All study foods will be produced in the Valid Nutrition factory in Malawi that is officially recognized as a UNICEF approved supplier for RUTF. The Factory is supplying the Ministry of Health of Malawi since 2005 and has produced study foods for several published studies.

**Table5: Composition of the study therapeutic food**

|                         | FSMS- RUTF | MSMS-RUTF | P-RUTF |
|-------------------------|------------|-----------|--------|
| Total content (g)       | 100.0      | 100.0     | 100.0  |
| Content without MN (g)  | 98.0       | 98.0      | 98.4   |
| Cost (US\$)*1           | 0.13       | 0.17      | 0.26   |
| Energy (kcal)           | 520.0      | 520.0     | 526.8  |
| Protein (g)             | 15.6       | 15.6      | 14.7   |
| Fat (g)                 | 34.3       | 34.5      | 33.1   |
| Carbohydrate(g)         | 42.1       | 40.7      | 46.6   |
| Fiber(g)                | 5.0        | 5.0       | 1.5    |
| Sodium (mg)             | 5.3        | 56.3      | 258.1  |
| Potassium (mg)          | 1155.8     | 1155.8    | 1140.0 |
| Calcium (mg)            | 437.8      | 437.8     | 328.6  |
| Phosphorous (mg)        | 446.0      | 446.0     | 370.0  |
| Magnesium (mg)          | 166.8      | 100.1     | 86.0   |
| Iron (mg)               | 60.0       | 60.0      | 12.0   |
| Zinc (mg)               | 20.6       | 20.6      | 11.1   |
| Copper (mg)             | 1.4        | 1.4       | 1.7    |
| Selenium (ug)           | 20.0       | 20.0      | 17.5   |
| Iodine (ug)             | 82.3       | 82.3      | 100.0  |
| Vit A-RAE (ug)          | 995.0      | 995.0     | 910.0  |
| Vit D (mcg)             | 15.0       | 15.0      | 16.0   |
| Vit E (mg)              | 40.7       | 40.7      | 20.0   |
| Vit K (ug)              | 41.9       | 41.9      | 21.0   |
| Thiamin (mg)            | 1.5        | 1.5       | 0.6    |
| Riboflavin (mg)         | 2.8        | 2.8       | 1.8    |
| Vit C (mg)              | 329.0      | 329.0     | 53.0   |
| Vit B6 (mg)             | 3.0        | 3.0       | 0.6    |
| Vit B12 (ug)            | 4.3        | 4.3       | 1.8    |
| Folate (ug)             | 200.0      | 200.0     | 210.0  |
| Vit B3 (mg)             | 18.8       | 18.8      | 5.3    |
| Vit B5 (mg)             | 4.5        | 4.5       | 3.1    |
| Vit B7 (ug)             | 60.0       | 60.0      | 65.0   |
| n-6 FFA                 | 5.8        | 3.4       | 4.8    |
| n-3 FFA                 | 0.5        | 0.2       | 0.1    |
| n6 (%/energy)           | 10.0       | 5.9       | 8.1    |
| n3 (%/energy)           | 0.8        | 0.3       | 0.1    |
| Phytic/zinc molar ratio | 3.3        | 2.2       | 2.2    |
| Phytic/Fe molar ratio   | 1.0        | 0.6       | 1.9    |

\*1: The Cost is not included MNP

The cost was calculated using price list from Valid Nutrition

## 2.5.6 Statistical analysis

### 2.5.6.1 Acceptability trial

For the acceptability trial, descriptive analyses will be performed and used for the conclusion on acceptability and tolerance. The conclusion will be made based on fulfilment or not of the set acceptability criteria including sufficiency of intake and frequency of side effects. For the conclusion on children preference, comparison of the median score obtained for each organoleptic characteristics will be made.

### 2.5.6.2 Efficacy trial

#### 2.5.6.2.1 Statistical analysis strategy

Data will be analysed by a statistician blinded as to type of food of the different group allocation. Both the intention-to-treat (ITT) and Per Protocol (PP) analyses will be used for data analyses. However, as per the recommendation of the CONSORT group, in case of opposition between conclusions from the ITT and PP analyses, the final conclusion will be based on PP analyses as ITT analyses inflate type-I error.

Appropriate quantitative methods will be used to provide answers to the study questions. As recommended by Piaggio et al. of the CONSORT (Consolidated Standards of Reporting Trials) group, the assessment of non-inferiority, the confidence interval approach will be used for the interpretation [98]. The figure 1 below illustrates the interpretation.

**Figure.** Possible Scenarios of Observed Treatment Differences for Adverse Outcomes (Harms) In Noninferiority Trials

[figure not shown]

Error bars indicate 2-sided 95% confidence intervals (CIs). Tinted area indicates zone of inferiority. A, If the CI lies wholly to the left of zero, the new treatment is superior. B and C, If the CI lies to the left of  $\Delta$  and includes zero, the new treatment is noninferior but not shown to be superior. D, If the CI lies wholly to the left of  $\Delta$  and wholly to the right of zero, the new treatment is noninferior in the sense already defined, but it is also inferior in the sense that a null treatment difference is excluded. This puzzling case is rare, since it requires a very large sample size. It can also result from having too wide a noninferiority margin. E and F, If the CI includes  $\Delta$  and zero, the difference is nonsignificant but the result regarding noninferiority is inconclusive. G, If the CI includes  $\Delta$  and is wholly to the right of zero, the difference is statistically significant but the result is inconclusive regarding possible inferiority of magnitude  $\Delta$  or worse. H, If the CI is wholly above  $\Delta$ , the new treatment is inferior.

\*This CI indicates noninferiority in the sense that it does not include  $\Delta$ , but the new treatment is significantly worse than the standard. Such a result is unlikely because it would require a very large sample size.

†This CI is inconclusive in that it is still plausible that the true treatment difference is less than  $\Delta$ , but the new treatment is significantly worse than the standard.

From Piaggio et al, JAMA, 2006(295):1152-1160.

For the comparison of survival after discharge from the therapeutic feeding programme, the Kaplan-Meier method will be used to construct survival curves, and the log-rank test and a Cox-regression model will be used

to compare the survival of children who recovered from SAM to that of the community control and assess the effect of some socio-economical and clinical characteristics such as gender, age at discharge, nutrition status at admission and at discharge, HIV status, tuberculosis, and phase angle on survival. Interactions of all the outcomes with the variables gender, form of SAM (oedematous or non-oedematous) and HIV status will be checked.

Given that the study will recruit over a short period of 6 months, no interim analyses will be conducted. However, the independent data monitoring committee will have the right to request Interim analyses if there are reports of several cases of serious side effects.

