### 2.3.2.2 Phase 2: efficacy trial

#### Primary hypotheses:

- 1 Recovery rate of children aged 6 to 23 months with SAM treated with FSMS-RUTF is > 75% and is not inferior to that of children with SAM of the same age treated with MSMS-RUTF nor to that of P-RUTF with the fixed non-inferiority margin being 10%.
- 2 Recovery rate of children aged 24 to 59 months with SAM treated with FSMS-RUTF is > 75% and is not inferior to that of children with SAM of the same age treated with MSMS-RUTF nor to that of P-RUTF with the fixed non-inferiority margin being 10%.

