#### 2.5.1.2 Efficacy trial

As stated in the hypotheses the main study will be a 3 group statistician blinded, randomized and controlled, parallel groups, **efficacy** non-inferiority trial. Because the participants will be able to distinguish the different RUTFs based on colour and mouth feel, participants will not be blinded. We will use the day care approach to ensure that children eat only the RUTF of the group to which they have been assigned. No study food will be taken home and the intake will be supervised by study enumerators who will in person feed the children.

The principal endpoints for the efficacy trial are:

1. Recovery rate
2. Mean weight gain
3. Mean time to recovery
4. Mean height gain
5. Percentage of body fat mass at recovery

6. Mean phase angle
7. Prevalence of anaemia
8. Incidence of deaths after discharge

The definition of principal endpoints is given below

(a) Recovery rate

The recovery rate will be measured as a percentage of those children who are discharged cured from the OTP programme divided by the total number of children who exit from the programme

$$\text{Recovery rate} = \frac{\text{No. children discharged Cured}}{\text{Total No. of Exit}} \times 100$$

(b) Average weight gain

The average weight gain will be measured as the mean of the growth velocity expressed in g/kg/day of individual children calculated as follow:

$$\text{Weight gain} = \frac{\text{Discharge weight (g)} - \text{Admission weight (g)}}{\text{Admission weight (kg)} \times \text{Length of stay (days)}}$$

$$\text{Average weight gain} = \frac{\Sigma \text{ weight gains}}{\text{Total children}}$$

(c) Average time to recovery or Length of stay

The average length of stay (LOS) is the mean of the LOS expressed in days of individual children calculated as follow:

$$\text{Average LOS} = \frac{\Sigma (\text{Discharge date} - \text{Admission date})}{\text{Total of children}}$$

(d) Average height gain

The average height gain is the mean of the height gain expressed in centimetres of individual children calculated as follow:

$$\text{Average height gain} = \frac{\Sigma (\text{Height 3 months after discharge (cm)} - \text{Admission height (cm)})}{\text{Total of children}}$$

(e) Prevalence of anaemia

The prevalence of anaemia will be expressed in percentage and calculated as follow

$$\% \text{ anaemia} = \frac{\text{n haemoglobin} < \frac{11.0\text{g}}{\text{dl}} * 100}{\text{total children with results}}$$

(f) Incidence of death after discharge

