### 2.5.4.3 Efficacy trial

#### 2.5.4.3.1 Treatment approach

RUTF is mostly used for the outpatient management of SAM and children are normally fed with RUTF by their main caregiver at home. However, to ensure that the research team has full control over the daily RUTF intake of study children, **a day care approach** will be used. The use of the day-care approach will eliminate the potential effect of operational constraints such as sharing, or sale of RUTF and inappropriate intake such as mixing RUTF with other foods that dilute energy and micronutrient densities. Although the use of the day-care approach may increase absenteeism, it will help to categorize children into those who strictly adhered to the protocol and those who did not adhere. It will also help to quantify the average daily intake from RUTF at individual level during the whole period of nutrition rehabilitation. An attempt will be made to capture the intake of other foods that children may eat at home in the evening.

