## **2.8 Risks and discomforts**

Similar products have been used in Zambia and Democratic Republic of Congo in children of same age with the same health condition. There was no particular serious side effect observed. Thus, in the present study there will be minimal risk to the children. The following are the potential risks and the steps that will be taken to minimize these risks:

- The risk of raw and processed food material contamination with bacteria that can cause diarrhoeal illness. Samples will be analysed to ensure that there is no contamination before the food is dispatched at study sites.
- Food allergies and food sensitivities: allergic reaction to the consumption of peanut has been reported in some countries but not in Malawi. If the children have history of food allergy, they will not be asked to participate.
- Suppression of appetite has been reported for some types of legume and cereal based RUTFs. As per our experience in Zambia and DRC, no such effect occurred with the use of SMS-RUTF and therefore we are not expecting to see this effect in Malawi. However, if this does happen to the children, they will be immediately withdrawn from the study and referred to the health facility for the standard treatment.
- Some children can have loose stools at the beginning of the nutrition therapy with RUTF, especially RUTF containing milk. Usually, the situation resolve spontaneously after one or two days and it does not result to any dehydration and does not delay recovery. In case the children do present such symptoms, they will be monitored carefully and given the appropriate additional treatment if required.
- Study foods have a higher level of iron than the standard food. There is a small risk of some abdominal discomfort at the start of the intake due to the level of iron in the food. However, such complaint was not registered in Democratic Republic of Congo where the RUTFs had the same level of iron. Thus, the risk of this effect occurring is low. If the effect does occur the children will be monitored carefully and given the appropriate additional or alternative treatment if required.

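### Letting per-protocol decide every ITT/PP conflict allows a non-randomised subset to overturn a failed randomised comparison

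*Protocol*

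**What the plan says.** Section 2.5.6.2.1 of the protocol states that "Both the intention-to-treat (ITT) and Per Protocol (PP) analyses will be used for data analyses". If they conflict, "in case of opposition between conclusions from the ITT and PP analyses, the final conclusion will be based on PP analyses". The reason given is "as ITT analyses inflate type-I error". The two primary hypotheses (section 2.3.2.2), one per age group, each ask for FSMS-RUTF recovery above 75% and for non-inferiority to MSMS-RUTF and to P-RUTF, "with the fixed non-inferiority margin being 10" percent.

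Three other places bear on who would be in each analysis:

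- Section 2.5.4.3.1, on the day-care approach, says that "it will help to categorize children into those who strictly adhered to the protocol and those who did not adhere". This is the only hint of what PP means; no definition is given.
- Section 2.8 says of children whose appetite is suppressed that "they will be immediately withdrawn from the study and referred to the health facility for the standard treatment". It adds that this effect did not occur with the previous SMS-RUTF and is not expected. For iron-related abdominal discomfort it says instead that "the children will be monitored carefully and given the appropriate additional or alternative treatment if required".
- Section 2.5.1.2 defines recovery as children discharged cured "divided by the total number of children who exit from the programme".

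**The concern.** The stated reason looks at one bias only. ITT can dilute a real difference, so letting PP decide is cautious when ITT passes and PP fails. The rule is written for any conflict, however. When ITT fails and PP passes, it sets aside the comparison that randomisation protects and rests the claim on children selected after randomisation.

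PP can be biased towards non-inferiority when exclusion depends on arm and outcome, and three features make that plausible here. Section 2.5.1.2 says participants can tell the foods apart. Adherence is judged from attendance and supervised intake, and intake can respond to the food: section 2.2 reports lower intake on the previous SMS-RUTF than on P-RUTF in both age groups (199 against 214 g/day, and 251 against 276 g/day). Appetite suppression, which section 2.8 says has been reported for some legume and cereal RUTFs, leads to withdrawal. If such children drop out of PP, the test arm loses some of its own failures, and both primary conclusions are exposed.

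**Working it through.** **1. The plan's own figure.** Table 2 assumes 75.5% recovery in every arm at 6-23 months, a 10-point margin, 80% power and 10% loss. The protocol's formula at one-sided 5% gives n = (1.645 + 0.842)² × 2 × 0.755 × 0.245 / 0.10² = 228.7, so 229 per arm. Allowing for loss, 229/0.9 = 255 or 229 × 1.1 = 252, against 250 stated. It reproduces. One-sided 2.5% gives 291 before loss and does not fit. At 24-59 months (88.2%) the formula gives 129, then 144 or 142, against 150 stated, which is on the safe side. The check below therefore uses one-sided 5%, with 250 × 0.9 = 225 and 150 × 0.9 = 135 children analysed per arm.

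**2. Scenario.** True ITT recovery is exactly at the margin, so a non-inferiority finding is a false one. A share w of the FSMS-RUTF arm only is withdrawn for a food effect. ITT counts these children as not recovered, in line with the all-exits denominator; PP drops them. The documents give no value for w, so it is varied from zero. Its top value, 10%, is the level below which phase 1 (section 2.5.1.1) still confirms tolerance as regards food-related withdrawals.

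**3. Formulas.** For 6-23 months:

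- PP recovery on FSMS-RUTF: q = 0.655/(1 − w)
- PP deficit: d = 0.755 − q
- SE = √[0.755 × 0.245/225 + q(1 − q)/(225(1 − w))]
- Chance that PP passes: Φ((0.10 − d)/SE − 1.645)

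At w = 10%: q = 0.655/0.90 = 0.728; d = 0.027; SE = 0.0424; Φ(0.07) = 53%.

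**4. Results, 6-23 months (75.5% against 65.5%, 225 per arm).** The last column comes from simulating the same scenario and requires observed PP recovery above 75% as well.

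| w | PP recovery, FSMS | PP deficit (points) | PP passes non-inferiority | and observed PP recovery > 75% |
|---|---|---|---|---|
| 0% | 65.5% | 10.0 | 5% | under 1% |
| 1% | 66.2% | 9.3 | 7% | under 1% |
| 2% | 66.8% | 8.7 | 9% | under 1% |
| 4% | 68.2% | 7.3 | 16% | about 1% |
| 6% | 69.7% | 5.8 | 25% | about 4% |
| 8% | 71.2% | 4.3 | 38% | about 10% |
| 10% | 72.8% | 2.7 | 53% | about 22% |

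With the two-sided 95% interval shown in the figure of section 2.5.6.2.1 (1.96 in place of 1.645), the non-inferiority column at w = 4%, 6%, 8% and 10% is 9%, 16%, 27% and 40%.

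**5. Results, 24-59 months (88.2% against 78.2%, 135 per arm, one-sided 5%).** Here q = 0.782/(1 − w), which is 81.5%, 83.2%, 85.0% and 86.9% at w = 4%, 6%, 8% and 10%. Simulation gives a PP pass in about 19%, 32%, 49% and 68% of trials (18%, 31%, 48% and 68% by the formula). Requiring observed recovery above 75% leaves these unchanged, because true recovery is above 75% even at the margin.

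**6. Requiring both analyses.** In the same simulations, a finding that needs both ITT and PP to pass occurs in about 5% of trials in each age group, at every w.

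**The case against.** The strongest reply has four parts.

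*The food effect is not expected.* Section 2.8 says so, section 2.2 calls the earlier intake difference clinically irrelevant, and section 2.3.1 allows the recipe to be refined after phase 1. The documents therefore point to a small w, and at 1% to 2% the pass rate at 6-23 months is only 7% to 9%. This stands as a limit on size. It is not complete reassurance: phase 1 studies children of 3 to 5 years without SAM, and section 2.2 expects the amino acid mixture to change the taste significantly.

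*PP is undefined.* A reader might infer that the protocol removes withdrawn children from PP. No section says so. It is inferred from the withdrawal wording and the adherence wording, and a SAP could count these children as failures. This stands. The precedence rule, however, is in the protocol, and it would still let any passing PP result override a failing ITT result.

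*Withdrawal is narrower than all food effects.* A reader might infer that every child with a side effect leaves the study. Withdrawal is stated only for appetite suppression; other effects are monitored, treated or referred.

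*The primary hypothesis has two halves.* A reader might take 53% as the chance that the primary conclusion flips at 6-23 months. It is the chance of passing the non-inferiority component. With the 75% condition applied to observed PP recovery, it is about 22%. The protocol does not say how that condition is judged; a stricter reading, with a lower confidence bound above 75%, would cut it to about 1%. The condition gives no such protection at 24-59 months.

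**Conclusion.** The concern holds as a defect in a stated decision rule. PP precedence guards against one direction of conflict and permits a false claim in the other. The rule should be changed, but the documents do not show that the error rate will in fact be inflated: that needs exclusions that occur, differ by arm and relate to outcome, and the protocol neither specifies nor expects these.

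The size is conditional. For 4% to 10% withdrawn in the FSMS-RUTF arm alone, the non-inferiority component passes falsely in 16% to 53% of trials at 6-23 months (about 1% to 22% with observed PP recovery above 75%), and in about 19% to 68% at 24-59 months, against a nominal 5%. These figures assume that every withdrawn child is uncured, that PP drops them and that ITT counts them as not recovered. If ITT instead used their later outcome on standard treatment, it could hide part of the failure too. Severity: should be fixed. The clinical rule for withdrawing a child is not at issue.

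**What to change.** In section 2.5.6.2.1, replace the precedence sentence with a rule that non-inferiority is claimed only if both the ITT and the PP intervals exclude the 10-point margin, and that disagreement is reported as inconclusive. This keeps the sponsor's intended protection when ITT passes and PP fails.

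Add that children withdrawn for a food effect count as not recovered in both analysis sets, consistent with the all-exits denominator in section 2.5.1.2. This removes the mechanism illustrated above, whatever else the PP definition contains.

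The cost is a few sentences and no new data. Requiring both analyses to pass lowers power slightly.
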